**Figure 1 F1:**
[figure not shown]
Personalized feedback. **(A)** Feedback shown to a male user, aged 18–20, with problematic use of alcohol using a subjective normative approach; screen 2 out of 4. **(B,C)** Feedback based on the FRAMES-Model (51); screen 3 and 4 out of 4.

**Figure 2 F2:**
[figure not shown]
“Diary”: self-monitoring and prompts. **(A)** Main screen of the app with newly activated modules highlighted by alert and an explanatory toast regarding not yet activated modules. **(B)** Encouraging prompt on the user's home screen. **(C)** User making diary entry.

**Figure 3 F3:**
[figure not shown]
“Diary”: feedback about consumption. **(A)** Feedback following an entry of a day not having used cannabis. **(B)** The calendar providing an overview of a user's recorded use of cannabis. **(C)** The statistics section providing an overview of the user's recorded mood while having used cannabis.

**Figure 4 F4:**
[figure not shown]
“Changing”: promoting motivation to change. **(A)** User has reflected on reasons for the use of substances and reasons for reducing the use of substances and starts to balance these in the motivational scale exercise. **(B)** User choses reasons for the use of substances and reasons for reducing the use of substances. **(C)** User receives feedback on personal reasons for substance use and reasons for changing one's substance use behavior.

**Figure 5 F5:**
[figure not shown]
“Relaxation”: skills-training with focus on emotions and behavior. **(A)** Overview of the exercises on breathing, and dealing with grief, anger, anxiety, and nightmares. **(B)** Examplary screen of the breathing exercise. **(C)** Examplary advice on how to cope with anxiety.

##### Referral Pathways

Participants with high scores on the AUDIT or the CUDIT-R that indicate an alcohol or cannabis use dependency, respectively, will receive personalized feedback that suggests and encourages to seek help, provides an example for a counseling center and, in the case of high alcohol use, the warning to “not stop consumption without professional help as it could lead to physical harm or danger (e.g., cramping).” Furthermore, the intervention provides information on addiction counseling centers in general and highlights reasons to seek support based on the criteria of ICD-10 (54). In a separate module (see Table 1; Figure 6A) a number to call a hotline for immediate assistance in crisis situations, selected counseling centers and a link to a further (German-wide) search list for addiction counseling centers, as well as additional relevant online applications, are provided.

**Figure 6 F6:**
[figure not shown]
Further modules. **(A)** Overview of referral pathways offered in the app. **(B)** Overview of badges acquired. **(C)** Example of explanatory content on the intervention exercises.

##### Cultural Adaptations

Critical to the development of the digital health intervention was the implementation of a number of culturally adapted elements. It follows Bernal and Sáez-Santiago's (42) guidelines on the practice of culturally competent psychology and is developed under consideration of both surface and deep structure dimensions (55). In line with these frameworks, the aspects of language, metaphors, the content, the concept, goals, methods, and the context as well as social, environmental, and psychological factors were considered when culturally adapting the intervention. The goal is to reduce (language) barriers and to maximize usability and acceptance of the intervention. The evaluation of above named focus group and consultation meetings with refugees and cultural mediators of the targeted countries of origin and experts from the field of refugee and addiction services lead to adapting single elements of the intervention:

The overall content of BePrepared has been formulated in easy language and translated into Arabic, English, German, Farsi, and Pashto by cultural mediators. These were instructed to translate content freely, e.g., sayings (module 3, see Table 1), metaphors, and concepts of distress (module 4, see Table 1), and in a spoken dialect rather than exact and possibly less comprehensible translations.

In a focus group with young refugees, we sketched a collection of motives for using and for not using substances and have integrated these in similar wording into the motivational scale exercise (module 2, see Table 1), a Motivational Interviewing technique (56).

In meetings with cultural mediators, we have e.g., identified values of the targeted culture (included in module 2, see Table 1), traditional sayings (implemented in the push notifications and module 3, see Table 1), adjusted wording, e.g., choosing the heading *positive thoughts* over the initial choice (*power-sentence)* or verbal ways to reject substance use in social situations (module 3, see Table 1), formulated suitable questions and answers implemented in an interactive quiz (based on the psychoeducative content, see Table 1), and adapted the information used for informed consent in terms of facilitated understanding.

In a focus group, experts from the field of refugee and addiction services highlighted the need for communicable data security, continuous reminders, a usage possible with limited internet connection and storage space, and a selection based on language skills rather than nationalities, which could all be implemented. The latter led to the separation of Group 1 (study participants) and Group 2 (app users), see under *Participants*.

The Arabic psychoeducative content was reviewed by an addiction counselor of Syrian origin to ensure that the thematic priorities had been remained after translation.

### Evaluation of the Digital Intervention

#### Study Design

We conduct a single-armed feasibility trial among 150 young refugees with problematic use of alcohol and/or cannabis in order to evaluate the intervention's usability and acceptability. Following the screening, participants will receive a digital health intervention (DHI) for the reduction of problematic substance use, introduced by a personalized feedback and carried out over a 4-week time frame. Follow-ups take place after 4 weeks (t_1_), 3 months (t_2_), and 6 months (t_3_).

#### Study Outcomes

We adopt a mixed methods approach to establish feasibility and acceptability of the DHI for the reduction of problematic substance use for young refugees, with data collected as outlined below.

#### Primary Outcomes

##### Feasibility

The feasibility of the DHI for substance use reduction will be assessed using a self-constructed Programme Participation Questionnaire (PPQ) which you can find in full length in Appendix 1. See Figure 7 for an excerpt of its visualization in the application. Furthermore, we will quantitatively assess the use of the app through the app's meta-data log-files, collecting data on:

the rate of completion of the intervention (i.e., number of participants who access and complete the following aspects of the intervention: screening, feedback, minimum 10 min spent in three of the four main modules),the frequency and duration of the intervention use,the preferences in intervention use (i.e., modules of the smartphone intervention most frequently assessed and on which most time was spent), andthe number of times the smartphone app was assessed).

We hypothesize that the intervention is feasible and accepted by the target group.

**Figure 7 F7:**
[figure not shown]
Implementation of the follow-measurements in the app. **(A)** Entry screen. **(B)** Examplary item of the overall assessment on the app. **(C)** Example item on cultural sensitivity.

##### Acceptability

Acceptability, perceived usefulness, and user-friendliness of the DHI and study procedures will be assessed using above named Program Participation Questionnaire. Quantitative data will be collected to assess the quality of each module and the overall cultural appropriateness of the DHI (see *Assessments*).

#### Secondary Outcome

As a secondary outcome, we will assess the initial efficacy of the DHI by the change from baseline in severity of substance use, depressive symptoms, and symptoms of anxiety. Comparing post-intervention to baseline levels, we will quantify

the initial efficacy of intervention using a 30-day prevalence measure in line with the Epidemiological Survey of Substance Abuse (2018),the change in depressive symptoms with the Patient Health Questionnaire [PHQ-9; (57)], andthe change in symptoms of anxiety with the Generalized Anxiety Disorders Scale-7 (GAD-7; 54).

For an overview of all outcomes and associated measures, see Table 2.

**Table 2 T2:** Measures and assessment at points used in the study.

**Construct (Assessment)**	**Baseline (t_**0**_)**	**Follow-up (t_**1**_/t_**2**_/t_**3**_)**	**Sources of translations**
Sociodemographics^a^^,^ ^b^			See note 2
Age	x		
Gender	x		
Home country	x		
Living situation	x		
Residence status	x		
Occupational status (past and present)	x		
Level of education	x		
Family status	x		
Information on children	x		
Religion	x		
Socio-economic status	x		
Additional inclusion criteria			Arabic, English, Farsi, Pashto: own translations
Refugee background	x		
No current psychiatric or psychological treatment for use of alcohol and/or cannabis	x		
Escape-related information			See Note 2
Dates of escapes' beginning^a^^,^ ^b^	x		
Duration of escape^a^^,^ ^b^	x		
Duration of stay in Germany^a^^,^ ^b^	x		
Accompaniment during escape^a^^,^ ^b^	x		
Burdens of missing information on family and friends^b^	x		
Substance use			
Alcohol (AUDIT)	x		Arabic: Almarri et al. (58); Farsi: Noorbakhsh et al. (59); German: Dybek et al. (60); Pashto: own translations
Cannabis (CUDIT-R)	x		Own translations
30-day prevalence	x	x	Own translations
Confidence in change	x	x	Own translations
Medical Questionnaire (pregnancy, serious disease, medication, SUD)	x		Own translations
Depression (PHQ-9)	x	x	German: Gräfe et al. (61); Arabic, Farsi, Pashto: own translation
Anxiety (GAD-7)	x	x	German: Löwe et al. (62); Arabic, Farsi, Pashto: own translation
Smartphone Use	x		own translations
Program Participation Questionnaire^b^		x	own translations

*1*:

a *Standardized measures with the PREPARE and PrevDrop research consortia*;

b *Standardized measures with the the KS-Diagnostik project*;

*^c^see attachments for full questionnaire*.

*AUDIT, Alcohol Use Disorders Identification Test; CUDIT-R, Cannabis Use Disorders Identification Test-Revised; PHQ-9, Patient Health Questionnaire; GAD-7, Generalized Anxiety Disorders Scale-7*.

*2: German, English, Arabic, and Farsi translations were shared by the research project PrevDrop on the Prediction and prevention of dropout in research, diagnostics, and treatment with refugees (contact: [name], [contact], https://www.gesundheitsforschung-bmbf.de/de/prevdrop-vorhersage-und-pravention-von-dropout-in-forschung-diagnostik-und-behandlung-mit-9672.php). For Pashto, we use own translations*.

#### Participants

Study participants will be Afghan, Iranian, Iraqi, and Syrian refugees living in Germany. We will recruit participants with a multi-strategic approach in Germany (see *Recruitment*).

During the onboarding of the app, written informed consent will be obtained. A screening in form of an online questionnaire will determine up to *n* = 150 refugees for eligibility for study participation.

Inclusion criteria are:

age between 18 and 28 years;country of origin being Afghanistan, Iran, Iraq, or Syria;self-declared refugee background;hazardous/problematic use of alcohol and/or cannabis determined as described below;informed consent to participate in the study;agreement with the application's terms of use.

Participants identified as eligible after study participation screening will be assigned to Group 1 (study participants). Participants that violate inclusion criteria (1) to (4), but are older than 18 years of age, to still be able to download and use the app and to be assigned to Group 2 (app users). This is in order to foster the dissemination of the app and to prevent systematic discrimination and potentially negative attitudes toward the app usage due to perceived unfairness. Minors are neither eligible for study participation nor app use.

Exclusion criteria for study participation are an age of under 18 years, a country of origin other than Afghanistan, Iran, Iraq, or Syria, no self-declared refugee background, no hazardous/problematic alcohol- and/or cannabis-use or negated consent to the study participation or the app's terms of use, and a current participation in an in- or out-patient treatment for SUD. For promoting dissemination, an exception is the participation in a group intervention program on substance use disorder and trauma (contact [name] at [contact] for more information) which will be assessed during the screening and which takes place within the “PREPARE research consortium on the Prevention and Treatment of Substance Use Disorders in Refugees”.

#### Recruitment

We will apply a multi-strategic approach to recruit Syrian, Iranian, Iraqi, and Afghan refugees living in Germany. First, our strategy includes training keypersons (e.g., people working in refugee accommodation centers, information centers, psychosocial centers, addiction counseling centers, …). Keypersons are trained in a workshop on how to address members of the targeted group in person, according to principles of Motivational Interviewing (56). The workshop is complemented by a booklet, which can be found for download in German language at: https://www.katho-nrw.de/fileadmin/primaryMnt/KatHO/DISuP/BePrepared/Praxisbuch_201104.pdf. Second, we will adopt a snowball sampling approach, communicated to the targeted group by the trained keypersons, which suggest refugees to spread information on the study within their personal social network and community. Third, we will distribute multi-lingual advertising material (i.e., posters and flyers) in facilities frequented by refugees. Fourth, multiple online platforms (e.g., the webpages www.beprepared-app.de, www.sucht-und-flucht.de, Google Play Store …) will advertise the study and app. The download of the app via the Google Play Store (see https://play.google.com/store/apps/details?id=dai.com.prepare) will be free of charge, however, restricted to users currently residing in Germany. A list of study sites is available on the following webpage: https://www.katho-nrw.de/katho-nrw/forschung-entwicklung/institute/disup/forschungsprojekte/beprepared/.

#### Assessments

After obtaining informed consent and an eligibility screen on the app usage (minimum of 18 years of age), the baseline-measurement (t_0_) is scheduled. The baseline questionnaires will consist of items relating to sociodemographics, escape related information, a medical questionnaire on pregnancy, serious disease, medication and SUD, depression, anxiety, and smartphone use (see Table 2). Follow-up measurements are scheduled directly after the intervention (t_1_), as well as at 3-months (t_2_), and at 6-months (t_3_) follow-ups. Assessment and intervention take place on the participants' mobile devices and pending assessments will block further use of the app. A schedule of enrollment, intervention and assessment is shown in Figure 8.

**Figure 8 F8:**
[figure not shown]
Schedule of enrollment, interventions and assessment. Completed SPIRIT 2013 figure of recommended content of enrollment, interventions, and assessments. t_0_, baseline; t_1_, 4 weeks after baseline (post intervention); t_2_, 16 weeks after baseline; t_3_, 24 weeks after baseline.

To assess problematic use of alcohol and/or cannabis, all participants receive a screening using the Alcohol Use Disorder Test [AUDIT; (63)] and a from 6- to 12-months adapted version of the Cannabis Use Disorder Test-Revised [CUDIT-R; (64)] at baseline t_0_. The AUDIT is a 10-item screening tool that assesses individual alcohol consumption, with scores for each question ranging from 0 to 4 (e.g., *never* scoring 0, e.g., *less than monthly* scoring 1, e.g., *monthly* scoring 2, e.g., *weekly* scoring 3, and e.g., *daily or almost daily* scoring 4) and overall scores ranging from 0 to 40. Scores of 0 to 5 and 0 to 4 indicate a safe use for males and females, respectively, scores from 5 to 19 and 4 to 19 indicate problematic use for males and females, respectively, and scores of 20 or higher is likely to indicate alcohol dependence. The CUDIT-R consists of eight items, screens individual cannabis consumption, with scores ranging from 0 to 4 (e.g., *never* scoring 0, e.g., *less than monthly* scoring 1, e.g., *monthly* scoring 2, e.g., *weekly* scoring 3, and *daily or alm*ost daily scoring 4). For all genders, a score of ≥ 8 and <12 represents problematic use of cannabis. The Generalized Anxiety Disorders Scale-7 [GAD-7; (65)] assesses symptoms of anxiety and consists of seven items, each scored from 0, *not at a*ll, to 3, *nearly every day*. Despressive symptoms are assessed with the Patient Health Questionnaire [PHQ-9; (57)], a screening tool that consists of nine items, as well as the GAD-7 items each scoring from 0, *not at all*, to 3, *nearly every day*. For the sources of translations see Table 2.

##### Study Adherence

In order to lower the risk for dropout, participants will be informed on the study procedure including the time needed to complete the digital health intervention and the follow-up measurements, and on incentives. Group 1 will receive a €15 gift card as a reward for their participation after completing measurement t_1_, t_2_, and t_3_. Group 2 will participate in a tombola with a minimum one in ten chance of winning a €15 gift after completing the measurements at t_1_, t_2_, and t_3_.

There are regular reminders in form of push notifications with the goal to draw attention to unused intervention components, missed diary entries, and the follow-up measurements (see Figure 2B). Study adherence will be assessed through the app's meta-data log-files which give information on the frequency and duration of intervention use.

#### Sample Size

In this Stage I clinical feasibility trial the emphasis lies on examining feasibility and acceptability of the intervention as well as on a first preliminary estimate of the intervention's efficacy. For this purpose a sample size of at least *n* = 150 is targeted. To be assessed for eligibility: *n* = 450; to be allocated to trial: *n* = 150; to be analyzed at t1: *n* = 150. While there is little to no literature on dropout rates in refugee populations (66), a literature review by Swift and Greenberg (67) shows highly heterogenous dropout rates in studies on psychological treatment, ranging from 0 to 74.23%, with a weighted drop out rate of 19.7%. Regarding digital interventions, a review of internet-based treatment for psychological disorders shows an average dropout of 31% (ranging from 2 to 83%) (68) and a more recent systematic review and meta analysis on studies of apps for depressive symptoms shows dramatic dropout rates of almost 50% when accounting for bias (69). Hence, the present intervention's dropout rate istself will be a strong indicator for the study's feasibility.

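### The sample size section carries 150 enrolled through to 150 analysed at t1 despite the dropout rates it cites; this cannot hold for the follow-up questionnaire behind the acceptability outcome

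*Protocol article*

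**What the plan says.** Under Sample Size, the protocol article says that "a sample size of at least *n* = 150 is targeted" and then gives the planned flow: 450 assessed for eligibility, followed by "to be allocated to trial: *n* = 150; to be analyzed at t1: *n* = 150". The next sentences review dropout elsewhere. Studies of psychological treatment are described as "ranging from 0 to 74.23%, with a weighted drop out rate of 19.7" per cent. Internet-based treatment averages 31% (range 2 to 83%). Apps for depressive symptoms show "dramatic dropout rates of almost 50% when accounting for bias". The section notes that little is known about refugee populations and concludes that dropout will itself be informative about feasibility.

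Under Participants, the screening "will determine up to *n* = 150 refugees for eligibility for study participation".

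Feasibility and acceptability are the two primary outcomes. Feasibility uses the Program Participation Questionnaire (PPQ) together with log-file measures, among them the completion rate. For the other primary outcome the text is: "Acceptability, perceived usefulness, and user-friendliness of the DHI and study procedures will be assessed using above named Program Participation Questionnaire". Table 2 marks the PPQ in the follow-up column (t1/t2/t3) and not at baseline. Statistical Analysis plans descriptive analyses, confidence intervals for use of the main modules and for the completion rate until t1, and linear mixed models for substance use, GAD-7 and PHQ-9. Limitations acknowledges in general terms that bias from systematic dropout cannot be ruled out.

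**The concern.** A plan that treats dropout as one of its results cannot also set it at zero in its participant flow. Setting analysed equal to allocated, directly before dropout figures of a fifth to a half, gives the reader a t1 number that the cited evidence does not support. The two wordings for 150 make this worse. If 150 is a minimum, recruitment could continue to offset losses; if it is a maximum, it could not.

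What is at stake is mainly the acceptability outcome. A person lost before follow-up still leaves log-file data and can be counted as a non-completer, but leaves no PPQ answers. Those who like the app are plausibly more likely to be present and answering at follow-up, so a responder-only acceptability figure would tend to be favourable. The stated 150 hides both the smaller number behind that figure and the selection.

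**Working it through.** **Inputs.** Allocated 150 and analysed at t1 150 (Sample Size). Dropout d of 19.7%, 31% and almost 50%, the last taken as 50% (Sample Size). PPQ at follow-up only (Table 2). Two assumptions are mine: a 95% Wald interval at p = 0.5 as a yardstick, since the article states no precision or power target; and, for the bounds, that 80% of PPQ responders rate the app acceptable.

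**1. The plan's own figure.** Implied loss = 1 − 150/150 = 0%. The article gives no derivation of 150 itself, so only the flow from 150 to 150 can be checked.

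**2. Expected number with t1 questionnaire data,** n = 150 × (1 − d):
- 19.7%: 150 × 0.803 = 120.45, about 120
- 31%: 150 × 0.69 = 103.5, about 104
- 50%: 150 × 0.50 = 75

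Only the lower ends of the cited ranges come close to the stated figure: 0% gives 150 and 2% gives 147. The upper end, 83%, gives 25.5.

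**3. The same in reverse.** To have 150 answering at t1 would need 150/(1 − d) enrolled: 187, 218 or 300. A maximum of 150 excludes this.

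**4. Precision,** half-width = 1.96 × √(0.25/n):
- n = 150: 8.0 points
- n = 120: 8.9 points
- n = 104: 9.6 points
- n = 75: 11.3 points

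**5. Selection.** Let r be the share responding and 0.80 the acceptance among responders. If every non-responder would reject the app, acceptance among all enrolled is 0.80r. If every one would accept it, acceptance is 0.80r + (1 − r). Over 150 enrolled:

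| Responders | Worst case | Best case |
|---|---|---|
| 120 | 96/150 = 64% | 126/150 = 84% |
| 104 | 83.2/150 = 55% | 129.2/150 = 86% |
| 75 | 60/150 = 40% | 135/150 = 90% |

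With 75 responders, a reported 80% is compatible with anything from a minority to a large majority of those enrolled.

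**6. Which outcomes are affected.** Log-file measures and the completion rate until t1 need no t1 questionnaire, so all 150 can form the denominator. A linear mixed model can retain people who have baseline data only. The PPQ has no baseline value and no log-file substitute. The shortfall therefore applies to questionnaire data at t1, and above all to the PPQ.

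**The case against.** The strongest reply is that 150 analysed at t1 means an all-enrolled analysis set. For log-file outcomes, the completion rate and the mixed models this stands. A reader might infer that the trial fails to deliver its stated size for every outcome; the article does not support that.

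A reader might also infer that satisfied survivors could confirm the hypothesis ("We hypothesize that the intervention is feasible and accepted by the target group") at any level of dropout. That goes too far as well. The hypothesis joins feasibility to acceptance, completion is a listed feasibility measure, and Sample Size names dropout as an indicator of feasibility, so heavy loss would count against it. No numerical success limit is printed, but one may stand in the full protocol or the SAP, and its absence from an article is not an error. The share retained in the cited app review would in any case be a poor basis for such a limit: completion here requires screening, feedback and at least 10 minutes in three of the four main modules, which is a different quantity from staying in a study.

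Three further points reduce the size of the concern without removing it.
- The cited rates come from other populations, their definitions of dropout cannot be seen, and their ranges are very wide.
- Table 2 lists the PPQ under all three follow-ups, so someone who misses t1 might still answer later.
- Under Study Adherence, gift cards, reminders and advance information are planned to limit loss. Pending assessments also block the app, but that presses mainly on people who still want to use it.

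The general caveat in Limitations is not tied to the PPQ and does not reconcile the 150-to-150 flow.

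**Conclusion.** The concern holds for questionnaire data. The stated flow assumes zero loss, contradicts the evidence cited beside it, and rests on a 150 that is both a minimum and a maximum. At the three average rates cited, about 75 to 120 of 150 would supply t1 questionnaires. This range is indicative, since it assumes that dropout in the cited reviews translates into missing t1 questionnaires here.

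The loss of precision is moderate: 0.9 to 3.3 points of half-width at p = 0.5. With no power or precision target stated, it cannot be called a loss of power. The more important consequence is that acceptability would rest on a selected group of responders. How far that could move the result depends on the response rate and on the assumed 80%; the PPQ itself is not shown, so a yes/no acceptability result is also an assumption.

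**What to change.** Keep 150 enrolled and make three changes of wording.

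1. Use one phrase for the 150, either as a minimum or as a maximum, in both Sample Size and Participants.
2. Replace the single t1 figure with two. All 150 enrolled are the denominator for log-file feasibility outcomes, including the completion rate. About 75 to 120 are expected to give t1 questionnaire data, with 95% half-widths of about 11.3 to 8.9 points at p = 0.5 and a note that the rates are borrowed from other populations.
3. In Statistical Analysis, report PPQ acceptability among responders together with the response rate and with worst- and best-case bounds over all enrolled Group 1 participants. Counting every non-responder as not accepting should appear only as the lower bound, because as a single headline imputation it would be open to dispute.

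No extra participants or measurements are needed. The price is a smaller stated n for the questionnaire outcomes and a less favourable acceptability statement. The change should be made before results are seen, since a choice of denominator made afterwards carries less weight.
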